**Methods/Design:**

This study will be an unblinded, randomized controlled trial with 110 participants comparing a 6-week program that includes self-management support, pain science education and exercise to a wait-list control. The primary outcome will be function measured by the Short Musculoskeletal Function Assessment - Dysfunction Index. Secondary outcomes will include pain intensity measured by a numeric pain rating scale, pain interference measured by the eight-item PROMIS pain interference item-bank, how much patients are bothered by functional problems measured by the Short Musculoskeletal Function Assessment - Bother Index, catastrophic thinking measured by the Pain Catastrophizing Scale, fear of movement/re-injury measured by the 11-item Tampa Scale of Kinesiophobia, sense of perceived injustice measured by the Injustice Experience Questionnaire, self-efficacy measured by the Pain Self-Efficacy Questionnaire, pain sensitivity measured by pressure pain threshold and cold sensitivity testing, fatigue measured by a numeric fatigue rating scale, pain neurophysiology knowledge measured by the Neurophysiology of Pain Questionnaire, healthcare utilization measured by number of visits to a healthcare provider, and work status. Assessments will be completed at baseline, 7 and 18 weeks. After the 18-week assessment, the groups will crossover; however, we anticipate carry-over effects with the treatment. Therefore, data from after the crossover will be used to estimate within-group changes and to determine predictors of response that are not for direct between-group comparisons. Mixed effects modelling will be used to determine between-group differences for all primary and secondary outcomes. A series of multiple regression models will be used to determine predictors of treatment response.

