#### Secondary objectives

This study will test the hypotheses that people with chronic pain experience greater pain intensity, pain interference, self-efficacy, catastrophic thinking, fear of movement/re-injury, pain neurophysiology knowledge, bother by difficulty with functional activities, fatigue, depressive symptoms, healthcare utilization and work status with COMMENCE in comparison to a wait-list control after 18 weeks.This study will compare the change in outcomes demonstrated by the wait-list group during their treatment period (18 to 36 weeks) to the change demonstrated during the wait-list period (0 to 18 weeks).This study will estimate whether the impact of the intervention is maintained over an intermediate follow-up term (18 to 36 weeks) in the treatment group.This study will determine whether the estimate of the magnitude of the effect is influenced by an 18-week delay.This study will identify demographic, psychological or psychophysical variables that are predictive of treatment response.

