**Fig. 1 Fig1:**
[figure not shown]
Study flow diagram

Between-group comparisons (objectives 1 and 2) will be limited to the 0- to 18-week period prior to the wait-list group receiving treatment. However, an 18- to 36-week period was added for ethical reasons (that is, the wait-list group will receive the treatment) and to allow four additional analyses to address objectives 3 to 6.

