^a^In the absence of an established MCID or MDC, change greater than half a standard deviation will be considered clinically meaningful [92]. In these instances, clinical data from Woodstock and Area Community Health Centre was used to establish the standard deviation

The primary outcome will be function as measured by the Short-Musculoskeletal Function Assessment - Dysfunction Index (SMFA-DI) [40].

Secondary outcomes will include the following:Short Musculoskeletal Function Assessment - Bother Index (SMFA-BI) [40]Numeric Pain Rating Scale (NPRS) [57]Numeric Fatigue Rating Scale (NFRS) [58]PROMIS Pain Interference Item Bank - 8 items [59]Patient Health Questionnaire (PHQ-9) [60–62]Pain Catastrophizing Scale (PCS) [30, 63, 64]Tampa Scale of Kinesiophobia - 11 (TSK-11) [65]Pain Self Efficacy Questionnaire (PSEQ) [66–68]Neurophysiology of Pain Questionnaire (NPQ) [69]number of health care visitswork status

Potential predictors of response will include baseline measures for each of the outcome measures listed above as well as:Post-traumatic Stress Disorder Checklist (PTSD-C) [70, 71]Injustice Experience Questionnaire (IEQ) [33]number of medications [72]disease count [72]

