To address objective #4 and estimate whether treatment effects are maintained beyond the 18-week assessment, the functional score (SMFA-DI) at the end of treatment (7 weeks) will be compared with the functional score at the 25- and 36-week assessments using a linear mixed effects model.

To address objective #5, the influence of the 18-week delay on the treatment effect will be determined by comparing the magnitude of treatment effect from the waist list group (from objective #3) with the estimate of the magnitude of treatment effect from the treatment group (from objective #1).

In order to address objective #6, each of the patient demographics, outcome measure scores, and objective measures will be tested for univariate relationship with SMFA-DI change score at 18 weeks (difference between SMFA-DI at 18 weeks and SMFA-DI at baseline) using a Pearson r for continuous variables and Chi squared tests for categorical variables. Variables with a significance of <0.10 will be included in the multivariate analysis so that no potential predictive variables will be overlooked. Potential predictor variables will be entered into a series of multiple regression models to determine which combination of baseline variables best predict changes in SMFA-DI.

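### The predictor analysis (objective 6) fixes the 0–18 week change, names no arm and has no treatment term, conflicts with the stated use of post-crossover data, and applies chi-squared tests to a continuous score

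*Protocol article*

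**What the plan says.** Under Secondary objectives, the last aim reads: "This study will identify demographic, psychological or psychophysical variables that are predictive of treatment response".

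The Analysis section carries this out in three steps.
- Each candidate is first "tested for univariate relationship with SMFA-DI change score at 18 weeks (difference between SMFA-DI at 18 weeks and SMFA-DI at baseline"). Which test is run depends on the type of candidate, and the plan assigns them thus: "using a Pearson r for continuous variables and Chi squared tests for categorical variables".
- The second step sets the bar for moving on to the joint models: "Variables with a significance of <0.10 will be included in the multivariate analysis".
- Multiple regression models then look for "which combination of baseline variables best predict changes in SMFA-DI".

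No step names an arm, a treatment term or a treatment-by-predictor interaction.

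Two other places describe the data for this objective differently. The Abstract (Methods/Design) says that "data from after the crossover will be used to estimate within-group changes and to determine predictors of response". Study design says that the 18–36 week period was added partly "to allow four additional analyses to address objectives 3 to 6".

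On candidates, the Self-report measures section states: "Potential predictors of response will include baseline measures for each of the outcome measures listed above". SMFA-DI heads that list. Study design and Wait-list control both place the wait-list arm's COMMENCE programme after the 18-week assessment.

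**The concern.** The objective asks who responds to COMMENCE. Up to week 18 the wait-list arm has not had COMMENCE, so its 0–18 week change is not a response to it. That arm's treated period, weeks 18–36, never enters the stated outcome, although two other places say that post-crossover data serve this objective. An analyst cannot follow all three statements.

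Three further features affect what a selected variable would mean.
- Without an arm contrast, a variable that only tracks natural course looks the same as one that changes the effect of treatment.
- A chi-squared test cannot relate a categorical predictor to a continuous score.
- Baseline SMFA-DI is tested against a difference that contains it with a minus sign.

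The Discussion intends to use the findings for prognosis and for tailoring care to people less likely to respond. A prognostic factor read as a response predictor would misdirect the second use.

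**Working it through.** **The three statements side by side**

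| Place | Data for objective 6 |
|---|---|
| Abstract, Methods/Design | Data from after the crossover |
| Study design | 18–36 week period added for objectives 3 to 6 |
| Analysis, objective 6 | Week 18 minus baseline only |

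The third row uses nothing collected after week 18, so it does not agree with the first two.

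**Inputs.** Sample size gives an SD of 23 at each time-point, 88 evaluable participants and a baseline-to-follow-up correlation of 0.82. That correlation is labelled 12 weeks and is taken here as the week-18 visit. The protocol states no figure for objective 6. Its allowance for drop-out reproduces (88 / 0.80 = 110), and 1:1 allocation gives 44 evaluable per arm.

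**Coupling of baseline with change.** With equal SDs and correlation r:

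corr(Y0, Y18 − Y0) = (r − 1) / √(2(1 − r)) = −√((1 − r)/2)

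At r = 0.82 this is −√(0.18/2) = −0.30, with no effect modification.

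The chance of passing the two-sided 0.10 screen, by Fisher's z, is Φ(atanh(|corr|)·√(n − 3) − 1.645):
- n = 44 (one arm): 0.3095 × 6.403 − 1.645 = 0.337, giving 63%.
- n = 88 (both arms): 0.3095 × 9.220 − 1.645 = 1.209, giving 89%.
- n = 88, allowing for the planned 10-point arm difference: the change SD is 23·√0.36 = 13.8 within arm and √(13.8² + 5²) = 14.7 pooled. The correlation falls to −0.282 and the pass rate to 85%.

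For r from 0.5 to 0.9 the correlation runs from −0.50 to −0.22. Selection at n = 88, before allowing for the arm difference, runs from about 100% down to 67%.

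**Prognostic factor or response modifier.** The protocol gives no effect sizes for predictors, so these are assumptions. A purely prognostic variable shifts change by k points per SD in both arms. A pure modifier does so in the treated arm only. The simulation used N = 88, 1:1 allocation, a within-arm change SD of 13.8, a treatment effect of −10 and a threshold of 0.10. Cells give the percentage of trials in which the variable is flagged.

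| k | Pooled screen: prognostic / modifier | COMMENCE arm only: prognostic / modifier | Arm-by-predictor interaction: prognostic / modifier |
|---|---|---|---|
| 3 | 60 / 25 | 41 / 40 | 10 / 25 |
| 5 | 93 / 46 | 75 / 74 | 11 / 49 |
| 7 | 99 / 68 | 94 / 94 | 10 / 74 |

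Pooling halves the modifier's slope and favours the prognostic variable. In the treated arm alone the two are flagged equally often. Only the interaction keeps the prognostic variable near the nominal 10%. It also flags baseline SMFA-DI in only about 10% of trials when there is no effect modification.

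**Chi-squared.** The outcome is defined as a numerical difference. Table 1 gives a 10-point minimal important difference for SMFA-DI, but the objective 6 text does not say that change is split there or anywhere else. As written, the test for sex, work status or diagnosis cannot be run on that outcome.

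**The case against.** A reader might infer that both arms are pooled. The text does not say so. Objective 6 concerns treatment response, which only treated people can show, and for the COMMENCE arm weeks 0–18 are treated time. On that reading the dilution disappears. This stands: pooling is one reading, and the defect is that the population is unstated and the window conflicts with two other sections.

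A reader might also infer that the analysis cannot identify anything useful. That goes too far. The Background frames the aim as testing whether known prognostic indicators predict response, and the Discussion speaks of prognosis for people entering the programme. A treated-arm model serves that aim. It does not show that a variable changes the effect of COMMENCE.

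On coupling, once baseline SMFA-DI is in the regression, modelling change or follow-up gives the other predictors identical coefficients. The problem is therefore confined to the univariate screen, to baseline SMFA-DI itself and measures correlated with it, and to models in which the screen leaves baseline out. Using follow-up as the outcome would not make baseline's own coefficient evidence of response either.

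Finally, objective 6 is the last of the secondary objectives. Nothing here touches objective 1, and the chi-squared problem concerns only categorical candidates in a screen.

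**Conclusion.** The point holds and should be fixed. The Analysis section conflicts with the Abstract and Study design on which data serve objective 6, and as written it leaves out the wait-list arm's treated period. Neither reading of the population isolates differential response: pooling dilutes it, and the COMMENCE arm alone gives predictors of outcome under treatment. Chi-squared tests do not fit the stated outcome.

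Baseline SMFA-DI correlates about −0.30 with change by construction and would be selected in about 63% of trials (n = 44) or 85–89% (n = 88) with no effect modification. These figures rest on the plan's equal SDs and its correlation of 0.82. The comparison of prognostic and modifying variables rests on assumed effects of 3 to 7 points per SD. Its direction follows from the design, but its size depends on those assumptions.

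The documents do not support saying that the analysis is worthless for prognosis or that the primary comparison is affected.

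**What to change.** 1. Reconcile the Abstract, Study design and Analysis sections. Define the objective 6 outcome over each participant's own treated window: weeks 0–18 in the COMMENCE arm and weeks 18–36 in the wait-list arm. For the wait-list arm, use week-18 predictor values where the visit schedule collects them (self-reported outcomes and the two psychophysical tests). Use baseline values for items that the protocol shows only at the initial assessment, such as recovery expectations. Label the results as prognostic under treatment, because this model has no untreated comparison.
2. Replace chi-squared with t-tests or ANOVA, or with regression terms for categorical predictors.
3. Force pre-treatment SMFA-DI into every model, and do not read its own coefficient as evidence of response.
4. Describe a variable as predicting response to COMMENCE only on the basis of an arm-by-predictor interaction in the randomised 0–18 week data, reported as exploratory.

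**Cost.** These are changes to the analysis text and need no new visits. Some wait-list predictors will be 18 weeks old when treatment starts. Interaction power is modest: about 49% at N = 88 for an assumed 5 points per SD tested at 0.10, and 25% to 74% for 3 to 7 points. Fewer response predictors will be claimed.

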Two treatment approaches for people with chronic pain that have not been included in traditional self-management programs and demonstrate improvements in function are pain neurophysiology education and individualized, goal-oriented exercises. Pain neurophysiology education has been defined as an educational intervention and is useful for “describing the neurobiology and neurophysiology of pain, and pain processing by the nervous system” [12]. Pain neurophysiology education is effective for individuals with chronic low back pain [12–14], whiplash-associated disorder [15] and chronic fatigue syndrome [16]. The influence of pain neurophysiology education on pain and function in other chronic pain conditions has yet to be investigated with a rigorous trial. Similarly, while most self-management programs encourage participation in exercise and physical activity; most have not included individualized exercise programs despite evidence of reduced disability for both musculoskeletal and neuropathic pain conditions with these approaches [17–21]. The intervention evaluated in this study will be self-management support that incorporates individualized exercises and pain neurophysiology education with a primary aim of improving function.

It is also not clear from previous research which persons are most likely to respond to chronic pain self-management support. Previous research has suggested a number of factors that may contribute to chronic pain and reduced functional rehabilitation outcomes. For example, high initial pain levels [22–24], female sex [23], lower expectations of recovery [25], low pressure pain thresholds [26], cold hyperalgesia [27–29], catastrophic thinking [30–32], sense of perceived injustice [33] and fear of movement or re-injury [34–36] have all been associated with chronic pain, disability, or poor rehabilitation outcomes. Some of these variables have been suggested as prognostic indicators with more consistency than others. This study will investigate whether some of these prognostic indicators help predict response to chronic pain self-management support with pain education and individualized exercise.

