#### Demographic information

The following information will be collected at the initial assessment and analyzed as potential covariates and predictors of response: age, sex, work status prior to symptom onset, length of time since symptom onset in months, diagnosis provided by a medical professional as reported by the patient, medication use, previous treatment received and expectations for recovery. Expectations for recovery will be assessed with two questions: i) Do you think your pain will improve? and ii) Do you think your functional abilities will improve?

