#### Psychophysical measures

Two psychophysical measures will be performed in order to estimate sensitivity of the nervous system both locally (at the point identified as “most tender”) and at two standardized locations (the area of skin over the muscle belly of the upper fibers of the trapezius and tibialis anterior).

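### Objective 6: the one-at-a-time P<0.10 screen of about 30 candidates lets in noise and can miss modest real predictors, so it does not serve its stated purpose

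*Protocol article*

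**What the plan says.** The Analysis section sets out a two-step procedure for objective 6. First, "each of the patient demographics, outcome measure scores, and objective measures will be tested for univariate relationship with SMFA-DI change score at 18 weeks", by Pearson correlation for continuous variables and chi squared tests for categorical ones. The filter and its reason follow: "Variables with a significance of <0.10 will be included in the multivariate analysis so that no potential predictive variables will be overlooked". Second, the survivors go into a "series of multiple regression models to determine which combination of baseline variables best predict changes in SMFA-DI".

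The candidates are listed in three places:
- Self-report measures: "Potential predictors of response will include baseline measures for each of the outcome measures listed above as well as" the PTSD checklist, the injustice questionnaire, the number of medications and the disease count.
- Demographic information: items are "analyzed as potential covariates and predictors of response: age, sex, work status prior to symptom onset, length of time since symptom onset in months", followed by diagnosis, medication use, previous treatment and two expectation questions.
- Psychophysical measures: pressure and cold tests, each at three sites.

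The Background takes a narrower starting point. It names eight factors from earlier research and says: "This study will investigate whether some of these prognostic indicators help predict response".

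**The concern.** A univariate screen followed by a search in the same data has two known faults. Each null candidate has a 10% chance of passing, so a long list almost guarantees false entries. A real predictor of modest size, or one masked by a correlated variable, can fail the filter and never reach the joint model. The second fault is the very thing the screen is said to prevent.

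The Discussion expects the predictor results to give practitioners useful information on prognosis. A predictor set and R² taken from this procedure at face value would look more reliable than they are.

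**Working it through.** **Plan's own figures.** The article gives no figure for objective 6 beyond the 0.10 threshold. The Sample size section gives 88 needed and 110 recruited: 88/(1 − 0.20) = 110. With 1:1 allocation, 88 is 44 per arm. The Analysis section does not say which arm or arms enter objective 6, and the Abstract says that post-crossover data will help determine predictors. I therefore show both n = 44 and n = 88.

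**Candidate count.**
- Baseline outcomes: SMFA-DI plus 11 secondary outcomes = 12.
- Further questionnaires and counts: 4, running total 16.
- Demographic items, with the two expectation questions counted separately: 9, running total 25.
- Psychophysical: one summary per test adds 2 (27). By site and material it is 3 + 3×2 = 9 (34). By side as well it is 18 (43).

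About 30 is a fair working figure.

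**False entries.** With k null candidates, the expected number passing is 0.10k. If they are independent, P(at least one) = 1 − 0.90^k.

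| k | expected to pass | P(at least one) |
|---|---|---|
| 27 | 2.7 | 0.942 |
| 30 | 3.0 | 0.958 |
| 34 | 3.4 | 0.972 |
| 43 | 4.3 | 0.989 |

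In simulation with 30 null candidates at pairwise correlation 0.3, the mean stays at 3.0, and at least one passes in 0.895 of runs (n = 44) or 0.887 (n = 88).

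**Missed predictors.** For a continuous predictor with true correlation r, Fisher's z gives a pass probability of about Φ(√(n−3)·atanh r − 1.645), plus a negligible opposite tail. For r = 0.20 and n = 44: √41 × 0.2027 = 1.298, and Φ(1.298 − 1.645) ≈ 0.36, or 0.37 with the other tail.

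| assumed r | n = 44 | n = 88 |
|---|---|---|
| 0.20 | 0.37 | 0.59 |
| 0.25 | 0.50 | 0.76 |
| 0.30 | 0.63 | 0.89 |
| 0.40 | 0.86 | 0.99 |

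Masking is worse. Take two predictors correlated 0.6, with coefficients 0.5 and −0.3. The second has marginal covariance −0.3 + 0.5×0.6 = 0 with the outcome. It passed in about 10% of simulated runs at either n, no more often than noise.

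**Optimism.** With 30 null candidates, the regression on those that pass shows a mean apparent R² of 0.24 (independent) or 0.18 (correlation 0.3) at n = 44, and 0.14 or 0.09 at n = 88. In new data the mean R² is below zero in all four settings.

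**The case against.** **The purpose clause.** The wording about overlooking nothing can be read as the reason for a looser threshold than 0.05, and not as a guarantee. That is fair, but a filter chosen for that purpose should serve it, and at these sample sizes it does so only for fairly strong predictors.

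**Stronger readings that the article does not support.**
- A reader might infer that no internal validation is planned. The article is condensed and simply describes none; a fuller plan may contain it. The point rests on the stated screen.
- A reader might infer that real predictors are dropped about half the time. That needs r = 0.25 and n = 44, and the article fixes neither. At n = 88 the miss rate for r = 0.25 is about a quarter.
- A reader might infer that a predictor set would be reported even if nothing predicted. The full null is unrealistic here. Baseline SMFA-DI is itself a candidate. With equal SDs and the stated correlation of 0.82, it correlates (0.82 − 1)/√(2(1 − 0.82)) = −0.18/0.60 = −0.30 with the change score. The null R² values therefore illustrate the optimism and do not forecast the result. How often a null variable ends up significant also depends on the unstated form of the regressions: with null candidates correlated at 0.3, simulations gave 32–35% of trials with any joint P<0.05, and about 70% after an assumed backward elimination at 0.05.

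Setting baseline SMFA-DI aside as a real predictor changes the screen result little: 29 null candidates still give 2.9 false passes, if they are unrelated to it.

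**Prespecification alone is not a cure.** This objection stands. Nine prespecified null terms have expected apparent R² of 9/(n−1): 9/43 = 0.21 and 9/87 = 0.10, close to the screened results with correlated candidates. An honest R² comes from the optimism correction, which could also be applied to the planned procedure. Prespecification removes the noise entries and the filter losses, and it uses the prior evidence that the Background cites.

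**Conclusion.** The point holds. The stated screen admits about three null variables of 30 (2.7 to 4.3 over the plausible counts) and lets at least one through in about 89–96% of trials if none predicts. That part needs only the threshold, the candidate count and an assumed correlation of 0 to 0.3 between candidates. The screen can also miss modest predictors. For assumed true correlations of 0.20 to 0.30, the pass rate is 37–63% at n = 44 and 59–89% at n = 88. These rates rest on assumed effect sizes and on a sample size that the article leaves open. As no correction for the selection is described, the predictor set and R² should be expected to be optimistic. The change is worth making. It concerns a secondary objective only and does not touch the primary between-group comparison.

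**What to change.** 1. Drop the univariate screen and fit one prespecified model. Its terms are baseline SMFA-DI and the eight factors named in the Background: initial pain, sex, expectations of recovery, pressure pain threshold, cold sensitivity, catastrophic thinking, perceived injustice and fear of movement.
2. Prespecify one summary each for expectations (two questions), pressure threshold and cold sensitivity (three sites each), so that the model stays at about nine terms.
3. Bootstrap the whole model-building procedure, and report optimism-corrected R² and shrunken coefficients. This is essential: nine terms leave 44/9 ≈ 4.9 to 88/9 ≈ 9.8 participants per term.
4. Report all other candidates listed under Self-report measures and Demographic information as exploratory.

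The cost is a change of analysis wording and a bootstrap; no data collection changes. The downside is a smaller, less favourable R² and the move of some listed candidates, such as self-efficacy, depressive symptoms and post-traumatic stress, out of the main model.
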